## Abstract

**Abstract:**

INSPIRE-PNRM+ (short for InterdiSciPlinary and InteRsectoral telemedIcal Evaluation, Coordination and Therapy at the ParkinsonNet RheinMain+) is an one-year, multicentre, interventional, open-label, two-arm, 1:1 randomized controlled trial (RCT) with the goal to improve the quality of care for Parkinson’s disease (PD) patients outside of a specialized clinical context. The study is funded by the German Innovation Fund mandated by the Federal Joint Committee (G-BA). The three core characteristics are (1) the employment of specially trained advanced practice nurses (APN) in an (2) interdisciplinary network and (3) the use of a specifically designed digital platform. This platform serves for documentation and communication, thereby helping patients receive individualized, guideline-based treatment and support in adapting their lives to the effects of the disease. 844 patients will be recruited. They will be divided into two groups: a “usual care” group which continues traditional care (i.e., usually consultation with a neurologist in private practice) vs. the “intervention” group which will have APN contact every three months or more frequently as needed over the period of 12 months. Patients’ quality of life serves as primary outcome measure, combined with a process evaluation and health economic analysis (cost-utility analysis (CUA)). Recruitment was ongoing at time of submission of this paper. This innovative study is the first in Germany where APNs are dedicated to PD care. The study may serve as blueprint when incorporating APNs into routine healthcare, similar to other countries.

**Trial registration:**

The study has been registered at www.clinicaltrials.gov, NCT06479083. Registered June 27, 2024. https://clinicaltrials.gov/study/NCT06479083?term=INSPIRE%20Parkinson&rank=1.

## Introduction

With a prevalence of around 0.35%, accounting for about 300.000 people in Germany [1], Parkinson’s disease (PD) is the second most common neurodegenerative disease after Alzheimer’s dementia, often leading to disability, the need for care, reduced quality of life and premature death.

Cardinal clinical symptoms include motor impairment with lack of movement (akinesia), muscle stiffness (rigidity), tremor and impaired postural stability with gait impairment with a risk of falls [2]. These typically start gradually and unilaterally; however, they soon evolve to bilateral involvement affecting day to day life and independence. Additional symptoms may include difficulties in speaking and swallowing, disturbances in autonomic function (e.g. blood pressure and digestion), sleep disorders, depression and mental impairment including dementia.

In addition to idiopathic Parkinson’s disease (PD), atypical parkinsonian syndromes are part of the broader spectrum of parkinsonian disorders. These include dementia with Lewy bodies (DLB), multiple system atrophy (MSA), progressive supranuclear palsy (PSP), and corticobasal degeneration (CBD). Compared to idiopathic PD, atypical parkinsonian syndromes generally exhibit a more rapid progression, involve additional brain regions, and show a limited or poor response to levodopa therapy [3].

Treatment of PD and atypical parkinsonian disorders remains symptomatic. There are no causative or neuroprotective therapies available, so patients are faced to combine multiple drugs from different drug classes, non-pharmacological interventions, and, in advanced stages, pump therapies or deep brain stimulation in some cases [4]. Especially as the disease progresses treatment becomes increasingly complex requiring multidisciplinary, personalized care that considers each patient’s medical, nursing and social situation [5]. Furthermore, with the forecast of change in the demographic age structure and increasing life expectancy, the expected number of people affected by a Parkinsonian disorder and the associated costs to the healthcare system are expected to rise further in the future [6, 7]. This poses an urgent unmet medical need.

However, integrated PD care networks are scarce making the access to coordinated multidisciplinary teams which provide specialized PD care a limited option. Instead, many patients experience lack of guidance in a complicated healthcare system [8].

Some countries such as the US, Australia, Canada and the Netherlands have incorporated nurse specialists/advanced practice nurses (e.g. PD nurses who are qualified at Master’s level) as part of their healthcare landscape [9]. In Germany, multidisciplinary teams dedicated to oncological disease have been successful in the last decade. However, there are less than a dozen specialised care networks for other disorders. To our knowledge there are none in Germany dedicated to PD which employ APNs.

In the attempt to improve healthcare provided under the statutory health insurance system and to change the landscape towards an optimized, effective, efficient and needs-based care for people with PD and atypical Parkinsonian syndromes we carefully planned the INSPIRE-PNRM+ study, funded by the German Innovation Fund mandated by the Federal Joint Committee (G-BA). The protocol is published herein.

The innovative protocol was developed through a close collaboration between the Sponsor, Key Opinion Leaders, representatives of the Patient Community, and National Regulatory Authorities. Methodological and statistical concerns were discussed, with an emphasis on selecting a primary outcome measure that focuses on the aspects of the diseases that are relevant and meaningful to patients and affect patient’s quality of life. The pathway to the study approval was facilitated by frequent communication between all parties, collaborative adaptation of study methodology and statistical approaches ensuring that feasibility and meaningfulness.

### Study aim of INSPIRE-PNRM + and study design

As the acronym suggests, aim of INSPIRE-PNRM + is the InterdiSciPlinary and InteRsectoral telemedIcal Evaluation, Coordination and Therapy at the ParkinsonNet RheinMain + in order to overcome insufficient integration of concomitant therapies into personalized treatment plans and interlinking treatment chains. This is an interventional, open-label, randomized controlled trial (RCT) with two arms, designed to assess efficacy over a one-year period, combined with a process evaluation and health economic analysis (cost-utility analysis (CUA)).

INSPIRE-PNRM + has three key core components:

(1) *Advanced Practice Nurses*.

The core component is the employment of advanced practice nurses (APNs), i.e. master level qualified-nurses with at least 2 years of professional experience in general nursing as well as a specialization on PD. For the purpose of this project, APNs received structured, focussed training (300 training hours) about clinical aspects, telehealth/telemedical care, general nursing, and APN-role development. This yielded in the qualification to initiate and conduct treatments according to current standards and guidelines and in the case of measures subject to prescription carry these out under telemedical supervision. Notably, across Germany there are yet no standardized training requirements for PD-dedicated non-physician healthcare providers. Since 2006, part-time training for Parkinson Nurses exists, which usually consists of four two-day modules and two weeks of clinical observation spread over one year. However, compared to this, APNs, as they are enrolled in the INSPIRE-PNRM+ programme, have much higher qualifications as described above.

(2) *Implementation of an optimized interdisciplinary and transsectoral network*.

The second central component is to integrate INSPIRE-PNRM+ into and thereby improve existing interdisciplinary and transsectoral outpatient care structures. INSPIRE-PNRM+ connects numerous care providers, i.e. 3 university hospitals (acute care), 1 rehabilitation/post-acute care hospital, 33 neurological specialists/consultant neurologists in private practice and, of course, 10 APNs. In a broader scope, there are a total of 56 partners with the local Parkinson Network which include allied health professionals (e.g. physiotherapists, occupational therapists, speech therapists), pharmacies, additional hospitals as well as PD patient organisations.

(3) *Implementation of a telehealth platform*.

The third central component of the project is the use of the telemedicine platform provided by the Zentrum für Telemedizin (ZTM) specifically for this purpose which contains an electronic case file and fosters communication and meetings between patients (e.g. for video calls) as well as between all healthcare providers (e.g. for authorization of proposed management decisions).

### Study oversight and ethics

The study is conducted in accordance with the International Conference for Harmonisation - Good Clinical Practice Guideline, the General Data Protection Regulator, and the Declaration of Helsinki. The study has been approved by the ethics committees of each participating center, primarily the University of Mainz (ref. no. 2024–17454). All participants gave written informed consent.

#### Study population and eligibility criteria

The study population consists of people affected by PD or an atypical parkinsonian syndrome. Inclusion and exclusion criteria are shown in Table 1. In accordance with the funding agreement, only individuals covered by statutory (public) health insurance were eligible to participate, while those with private insurance were excluded. Two statutory health insurance providers will supply data on the economic impact of the intervention through a Selektivvertrag (selective contract) agreement.

The study will enrol approximately 844 patients (see below). First patient in was in July 1, 2024.

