### Statistics: case number calculation

The PDQ-39, used as a measure of quality of life, is based on a Likert scale and can therefore be treated as providing metric-level data. To estimate the required sample size based on the research hypothesis, a two-sample t-test for independent groups was used to compare means. Cohen’s d served as the a priori effect size, reflecting the standardized mean difference. An approximated value of d = (5 − 2)/14.48 = 0.207 was used. The significance level was set at α = 0.05. According to Horváth et al. (2017), the minimally clinically important difference (MCID) for the PDQ-39 is −4.72 points (12). Based on this MCID, the assumed effect size, a statistical power of 80%, and an estimated dropout rate of 20%, the required total number of participants to complete the intervention was calculated to be 620. The sample size calculation was performed using G*Power (version 3.1).

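### The enrolment target of 844 cannot be derived from the article's own case number calculation (620 completers at 20% dropout give 775), and 620 does not follow from d = 0.207

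*Protocol article*

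**What the plan says.** The Abstract gives the target as "844 patients will be recruited". The section on study population and eligibility repeats it and sends the reader further down the article: "The study will enrol approximately 844 patients (see below".

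The only calculation further down is under Statistics: case number calculation. It uses a two-sample t-test with this effect size: "An approximated value of d = (5 − 2)/14.48 = 0.207 was used". On the error rate it says "The significance level was set at α = 0.05", without saying whether the test is one- or two-sided. It adds "a statistical power of 80" per cent and "an estimated dropout rate of 20" per cent, and it concludes that "the required total number of participants to complete the intervention was calculated to be 620". The number 844 does not appear in that section. The article mentions no further allowance, such as for clustering, subgroups or the health economic analysis.

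**The concern.** Enrolment, dropout and completers form one chain: any two of them fix the third. The article prints all three, and they do not agree. The cross-reference that should explain 844 leads to a calculation with a different result.

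This matters because recruitment is still open. Under Trial status the article reports more than 500 patients enrolled, so the target and the tolerable loss are live figures. At 25% attrition, for example, 844 × 0.75 = 633 patients would complete. That meets the stated 620, exceeds the planned dropout, and falls below the roughly 675 that 844 implies. The article does not let a reader say whether such a trial kept its planned power. The difficulty is greater because 620, the figure one would fall back on, does not reproduce from the stated effect size.

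**Working it through.** **Inputs.** From the case number calculation: difference 5 − 2 = 3 points, SD 14.48, d = 3/14.48 = 0.2072 (printed as 0.207), α = 0.05 with no sidedness, power 80%, dropout 20%, 620 completers. From the Abstract and the population section: 844 enrolled. Allocation is 1:1.

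**Step 1: from 620 to enrolment.**
- Correct inflation: 620/(1 − 0.20) = 775.
- Common shortcut: 620 × 1.20 = 744.
- Neither is 844. The gap from 775 is 844 − 775 = 69, too large for the word approximately to cover.

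**Step 2: back from 844.**
- Completers at 20% dropout: 844 × 0.80 = 675.2, about 675, which is 55 more than 620.
- Dropout that takes 844 to 620: 1 − 620/844 = 26.5%.
- If 620 already included dropout, completers would be 620 × 0.80 = 496, and 844 would be further away still.

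**Step 3: can 620 be reproduced?** The normal approximation per arm is n = 2(z_α + z_0.80)²/d², with z_α = 1.960 two-sided or 1.645 one-sided, and z_0.80 = 0.842. The totals below use the noncentral t distribution, which differs from this by at most 2 patients in total.

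| d | Sides | Completers | Enrolled (÷ 0.80) |
|---|---|---|---|
| 0.2072 | two | 734 | 918 |
| 0.207 | two | 736 | 920 |
| 0.2072 | one | 578 | 723 |
| 0.207 | one | 580 | 725 |
| 0.20 | two | 788 | 985 |
| 0.20 | one | 620 | 775 |

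The figure of 620 appears only with a one-sided test and d rounded down to 0.20. That route again gives 775 enrolled. The article also names an MCID of 4.72 points as a basis. Using it as the difference gives d = 4.72/14.48 = 0.326, which needs 298 completers and 373 enrolled two-sided, so it explains neither 620 nor 844.

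**Step 4: near matches to 844.** A one-sided test at d = 0.2072 with 85% power needs 672 completers, and 672/0.80 = 840. A two-sided test with d rounded up to 0.21 needs 714 completers, and the shortcut gives 714 × 1.20 = 857. The first contradicts the stated 80% power, the second changes the stated d, and both contradict 620.

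**Step 5: power at d = 0.2072.**

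| Completers | Two-sided | One-sided |
|---|---|---|
| 620 | 73% | 82% |
| 675 (844 less 20%) | 77% | 85% |

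**The case against.** The strongest reply is that 844 errs on the safe side. If 620 completers are what the trial needs, 844 exceeds the required 775 and tolerates a 26.5% loss instead of 20%. This stands as far as it goes: measured against the article's own completer figure, the target is not short. It settles the matter only if 620 is sound, and Step 3 shows that 620 does not follow from the stated effect size.

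A second reply is that a journal article condenses a fuller protocol, which may contain an allowance not printed here. That also stands. For instance, the baseline assessment comes before randomisation, and a loss of about 8% at that point (1 − 775/844) would link 775 to 844. The article does not say this, and the Abstract, which has the recruited patients divided into the two groups, weighs against it. The possibility means one cannot say that 844 has no derivation anywhere. It does not reconcile the three printed figures.

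A reader might also infer that the trial is underpowered. The article does not support that without qualification. Power falls below 80% only if the test is two-sided; if it is one-sided, 844 enrolled with 20% dropout gives about 85%.

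**Conclusion.** The point holds for this article: 844 cannot be reached from the calculation it refers to. The mismatch is 69 enrolled patients (844 against 775), or 55 completers (675 against 620), or 26.5% dropout against 20%. The direction is conservative relative to 620, but 620 itself reproduces only with a one-sided test and a rounded d. At the stated d = 0.207, the planned enrolment delivers about 77% power two-sided or 85% one-sided. Whether 844 is slightly short or more than enough therefore depends on a sidedness that the article does not give.

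These figures assume 1:1 allocation, an unadjusted two-sample t-test, α = 0.05, SD 14.48, and dropout of exactly 20%. Two stronger conclusions do not follow: that 844 lacks any basis in the full protocol, and that enrolment must rise.

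**What to change.** In the case number calculation:

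1. State whether α = 0.05 is one- or two-sided, as fixed in the approved protocol and not chosen now to suit 844.
2. Restate the completers from d = 0.207 at 80% power: about 734 to 736 two-sided, or 578 to 580 one-sided. If d = 0.20 was the value actually used, say so.
3. Inflate by 1/(1 − 0.20).
4. Link the result to 844 in one of two ways. Either name the allowance or dropout rate that leads there, or keep 844 and state what it delivers: about 675 completers at 20% dropout, with about 77% power two-sided or 85% one-sided at d = 0.207.

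Then use the same figures in the Abstract, the population section and the calculation.

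The cost is a few sentences and one rerun of the sample size software. Enrolment need not change if the achieved power is restated. Only if the test is two-sided and the sponsor wishes to hold 80% power at 20% dropout would the target become about 918 to 920, which is 74 to 76 more than 844. That is a design decision for the sponsor, not a correction this point demands.

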### Study centers/collaboration partners

The PNRM+ network fosters collaboration between numerous partners.

### Recruitment and patient involvement

Patients are recruited via personal correspondence, routine care appointments, and referrals. In addition, there is tremendous collaboration and support from patient organizations representing the Parkinson communities. 

The principal investigator at each study site is responsible for obtaining informed consent for each patient. All eligible patients who agree to participate in the study are provided with a full verbal explanation of the trial and the patient information sheet. This includes detailed information about the rationale, design, and personal implications of the study.

### Study intervention procedures

All patients undergo an initial comprehensive assessment by the APN of their health and care situation in their homes (baseline visit; see Figure 1). Assessments includes a motor exam (UPDRS), structured interviews regarding non-motor symptoms, the familial and professional social and psychosocial situation, the living and housing situation (including support structures, accessibility), and previous and current treatment and therapies, and standardized questionnaires including the International Consortium for Health Outcome Measurements (ICHOM) as part of the internationally established battery for recording the patient-centered evaluation, quality of life questionnaire (PDQ39). All assessments are carried out independently by the APN. Patients are then 1:1 randomized into either the intervention group or the control group. The control group does not receive further APN input until the final visit at 12 months. For patients from the intervention group the APN draws up a person-centered and evidence-based treatment plan. They ensure care is provided in line with requirements and guidelines or initiates appropriate measures in accordance with the treating neurologists within the specialized PNRM+. If the APN recommends a prescription for a subject, these are passed on to the treating neurologist (nVF4) in accordance with current legislation. The APN is responsible for monitoring the treatment plan, evaluates it quarterly in the follow-up (nVF6) and implements adjustments as necessary. The APN also recommends which level of care (private practice, board, hospital outpatient care) is deemed necessary to provide patients with the care they need without delay. 

Through the PNRM+ network the APN plans and coordinates the cross-sectoral initiation of necessary treatment steps and provides those involved with patient-relevant information (nVF8). APNs also have the opportunity to easily consult with a movement disorders expert from one of the University Medical Centers on an individual patient basis (nVF12) or initiate a geriatric/psychiatric board (nVF9; nVF10) if they notice a deterioration in the patient's state of health. Here, too, the APN can provide first aid on a situational basis. 

Telehealth-supported communication with patients plays a major role in the implementation of treatment plans. Thus, as part of disease education (nVF5), patients and their care givers receive comprehensive, needs-based, participatory advice and training on various aspects related to the disease, treatment or life situation including coping strategies tailored to individual needs from APNs. This allows patients sufficient time to ask questions, enabled “shared decision making” that consolidates health literacy and strengthened self-efficacy of patients. In addition to these care services, on-demand services are established with the intent that urgent health requests can be addressed by the APN making it obsolete to call the national emergency hotline (i.e, 112 equivalent to 911). 

At 12 months, both the intervention and the control group undergo a final visit to reevaluate the patient’s situation and disease parameters. These and other clinical measures will be analysed together with numerous health economic parameters (see Table 2) in order to answer the main question: did the additional innovative fusion of three components result in added value for patients?

### Statistics: case number calculation

The PDQ-39, used as a measure of quality of life, is based on a Likert scale and can therefore be treated as providing metric-level data. To estimate the required sample size based on the research hypothesis, a two-sample t-test for independent groups was used to compare means. Cohen’s d served as the a priori effect size, reflecting the standardized mean difference. An approximated value of d = (5 − 2)/14.48 = 0.207 was used. The significance level was set at α = 0.05. According to Horváth et al. (2017), the minimally clinically important difference (MCID) for the PDQ-39 is −4.72 points (12). Based on this MCID, the assumed effect size, a statistical power of 80%, and an estimated dropout rate of 20%, the required total number of participants to complete the intervention was calculated to be 620. The sample size calculation was performed using G*Power (version 3.1).

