One weakness of the study is the relative short intervention period of 12 months. A longer period would likely better reflect the impact of APN intervention in PD management and treatment. Second, the open-label character of this study may influence the reactions and behaviors of patients and healthcare providers leading to performance bias. Third, participants in the current study had early or mid-stage PD. Patients with concomitant dementia, defined by MOCA<19, did not meet inclusion criteria. Future studies focussing on these patients are needed, given that treatment then becomes even more complex and challenging for care-givers. 

In summary, the concept of the INSPIRE-PNRM+ study is novel for Germany, building on longstanding international experience where APN are integral part of PD care. Positive evaluation of this a new model of healthcare delivery, will provide the basis for long-term integration and implementation into standard care with APN as part of a multidisciplinary Clinical Care Team [17]. In parallel, standardized training opportunities tailored to the care priorities of PD-patients will be needed [13]. 

**Table 1 Tab1:** Inclusion and exclusion criteria

Inclusion criteria	Exclusion criteria
Age: 30–85 years	Profound dementia (MOCA < 19)
PD (ICD: G20.-) or atypical PD (ICD: G23.-), according to the current diagnostic criteria of the Movement Disorder Society	Severe depression
Resident of Saarland, Hesse and Rhineland-Palatinate (INSPIRE-PNRM+ region)	Psychoses or other psychiatric or medical comorbidities that could interfere with study participation (e.g. tumour diseases with limited life expectancy, dialysis requirement, etc.)
Ability to consent	Drug or alcohol addiction
Insurance cover with a public health insurance company	Pregnancy or breast-feeding
	Simultaneous participation in another interventional treatment study
	Illiteracy or insufficient language skills to complete the questionnaires
	Insurance cover with a private health insurance company

**Table 2 Tab2:** Key research questions

Research questions	Related outcome measures
Differences in the change in Parkinson’s-specific quality of life after 12 months	PDQ-39 sum index (primary endpoint)
Differences in the change in motor symptoms after 12 months	MDS-UPDRS, part 3
Differences in the change in disease-overarching quality of life after 12 months	EQ-5D-5 L

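### The 620 completers stated for 80% power do not follow from the stated d = 0.207 and α = 0.05, whether the test is one- or two-sided

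*Protocol article*

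**What the plan says.** All the inputs but one are in the protocol article under 'Statistics: case number calculation'.

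- Test: "a two-sample t-test for independent groups was used to compare means".
- Effect size: "An approximated value of d = (5 − 2)/14.48 = 0.207 was used".
- Level: "The significance level was set at α = 0.05", with no mention of one or two sides.
- Power and attrition: "a statistical power of 80%, and an estimated dropout rate of 20" per cent.
- Result: "the required total number of participants to complete the intervention was calculated to be 620", computed in G*Power.

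The same section also cites an MCID: "the minimally clinically important difference (MCID) for the PDQ-39 is −4.72 points". Allocation comes from 'Study intervention procedures': "Patients are then 1:1 randomized into either the intervention group or the control group". Planned enrolment is 844 (Abstract; 'Study population and eligibility criteria'). Table 2 words the primary research question without a direction: "Differences in the change in Parkinson’s-specific quality of life after 12 months".

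**The concern.** The section gives everything needed to recompute the sample size except the number of sides, and neither choice returns the printed answer. This is the article's only power justification for the primary endpoint. A reader who sees α = 0.05 without qualification, beside a research question about differences, will assume 80% power for a two-sided 5% test. Two things are at stake. If the test is two-sided, the stated power is too high. If it is one-sided at 5%, the false-positive rate in the favourable direction is twice the 2.5% of a two-sided test, and the article does not say so.

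**Working it through.** **Inputs.** Difference 5 − 2 = 3 points and SD 14.48, so d = 3/14.48 = 0.2072, printed as 0.207. α = 0.05, power 80%, equal arms.

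**Formula.** Normal approximation, per arm: n = 2(z_α + z_β)²/d², with z_β = 0.8416 and z_α = 1.9600 (two-sided) or 1.6449 (one-sided). The noncentral t, the approach G*Power takes, adds at most one patient per arm here.

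**Attempt to reproduce 620 at the stated d = 0.207** (d² = 0.042849)

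- Two-sided: 2 × (2.8016)²/0.042849 = 366.3, so 367 per arm and 734 in total. The t-test gives 368 per arm, 736 in total.
- One-sided: 2 × (2.4865)²/0.042849 = 288.6, so 289 per arm and 578 in total. The t-test gives 290 per arm, 580 in total.

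**Variants** (total completers for 80% power)

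| d | Sides | Normal | t-test |
|---|---|---|---|
| 0.2072 (unrounded) | two | 732 | 734 |
| 0.2072 (unrounded) | one | 578 | 578 |
| 0.207 (as printed) | two | 734 | 736 |
| 0.207 (as printed) | one | 578 | 580 |
| 0.21 | two | 712 | 714 |
| 0.21 | one | 562 | 564 |
| 0.20 | two | 786 | 788 |
| 0.20 | one | **620** | **620** |

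For d = 0.20, one-sided: 2 × (2.4865)²/0.04 = 309.1, so 310 per arm and 620 in total.

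**Other explanations**

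- *Dropout already included.* Dividing the d = 0.207 t-test totals by 0.8 gives 580/0.8 = 725 or 736/0.8 = 920. The section in any case describes 620 as completers.
- *MCID as the difference.* 4.72/14.48 = 0.326 needs 296 (two-sided) or 234 (one-sided).
- *Other powers and effect sizes.* A wider search that added dropout found totals near 620 (605, 613, 630). Each needs a power or effect size that the section does not use, and none equals 620.

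**Power for the 3-point difference.** Normal approximation, n per arm: power = Φ(d√(n/2) − z_α).

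- 620 completers (310 per arm): 0.207 × √155 = 2.577. Two-sided: Φ(2.577 − 1.960) = Φ(0.617) = 73%. One-sided: Φ(2.577 − 1.645) = Φ(0.932) = 82%.
- 844 enrolled less 20%: 844 × 0.8 = 675 completers, about 337.6 per arm. 0.207 × √168.8 = 2.689. Two-sided: Φ(0.729) = 77%. One-sided: Φ(1.044) = 85%.

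The noncentral t agrees to within about 0.2 percentage points.

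**Difference detectable with 80% power, two-sided:** 2.8016 × 14.48 × √(2/n) gives 3.26 points at 310 per arm and about 3.1 points at 337.6 per arm.

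**The case against.** The strongest reply is that the shortfall assumes a two-sided test that the section never specifies. Other wording in the article points in one direction: the goal is to improve care, the main question is whether patients gain added value, and the effect is written as 5 − 2 beside a signed MCID. With a one-sided test, 620 completers give 82% power at d = 0.207. The gap is then only rounding of d, on the conservative side, and the section does call its d approximate. The article is also condensed, so the full protocol or SAP may fix the sidedness. Finally, enrolment is 844 rather than 620, so the 73% applies only if attrition reaches 1 − 620/844 = 26.5%.

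Much of this stands. Two stronger readings are tempting, and the article supports neither:

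- *The trial is underpowered.* That holds only if the primary test is two-sided, and at the planned enrolment the gap is then about 3 percentage points.
- *The sponsor used a one-sided test with d = 0.20.* The exact match makes this probable, but the text says neither.

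The reply does not rescue the printed figure. It disagrees with the printed d under either choice of sides, so a statement of sidedness elsewhere would not reconcile the two.

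**Conclusion.** The figure of 620 is wrong as written. The stated inputs require 736 completers two-sided (734 with unrounded d) or 580 one-sided (578 unrounded). This needs no assumption beyond the section's own inputs and 1:1 allocation.

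The effect on power is conditional:

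- Two-sided 5% test: about 73% at 620 completers and about 77% at 675, against the stated 80%. This is the conventional reading of an unqualified α = 0.05 and fits the wording of Table 2, but the article does not confirm it.
- One-sided 5% test: about 82% at 620 and 85% at 675. Power is then sufficient, but the one-sided level is undisclosed in the article.

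All power figures are for an unadjusted t-test with SD 14.48 and a 3-point difference.

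**What to change.** State the sidedness of the primary test and the d actually entered, before the data are analysed, and print figures that reproduce from them.

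- **If two-sided, with enrolment left at 844:** 'about 675 expected completers after 20% dropout; 77% power for a 3-point difference (80% for about 3.1 points), two-sided α = 0.05, unadjusted t-test'. Give the 80% requirement as 736 completers for d = 0.207. The figure 734 belongs to the unrounded d, and at the printed 0.207 it gives just under 80%.
- **If one-sided:** say so, give the 5% one-sided level explicitly, and print either 580 completers for d = 0.207 or 620 for d = 0.20.

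The cost is wording in the sample-size section and, where needed, the SAP. No extra patients are needed. The downside is a slightly less favourable stated power if the test is two-sided, or an openly one-sided 5% level if it is not. Recruitment was still under way when the article was submitted, so the correction can be made before results are known.
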